### 8.11.2. *Missing data for secondary endpoints and baseline covariates*

For binary and normally-distributed secondary endpoints as well as baseline covariates with missing data, we will generate 10 completed datasets via a Multiple Imputation with Chained Equations (MICE) algorithm for the secondary and sensitivity analyses specified. MICE draws missing data values from a sequence of fully-specified regression

models. We will use logistic regression models for modeling missing binary data, and normal linear regression otherwise. The linear predictor for each regression model will include linear terms for the primary outcome (PDHD), all secondary outcomes, and all baseline covariates, in addition to first-order interactions with each intervention arm.

Once generated, we will use the 10 completed datasets to fit the appropriate analysis models, performing final aggregated estimation and inference using Rubin's rules.

For the primary analysis, we will impute any missing baseline covariates based on the following logic:

- If the patient is missing a value for the severe illness indicator, we will impute the value to 0 (not severe).
- If the patient is missing a value for discharge location, we will impute the value to 0 (home).

We expect minimal missing baseline covariates (<1%) so are choosing imputation rules that are designed around the most likely categories given a value is missing.

## 8.12. *Type 1 error rate*

Success is declared at the final analysis when all patients have observed their primary endpoint if the posterior probability of any care model relative to STS is greater than 0.991. This threshold was determined through simulation to assure the type I error is controlled at a 2.5% level (see Appendix). Specifically, we simulate 10,000 trials under the null scenario and find the threshold that controls overall 2.5% type I error (probability of declaring success under the null) across the simulated trials.

# 9. ETHICAL CONSIDERATIONS

## 9.1. *Data Safety and Monitoring Board*

The DSMB will provide oversight for the trial.

## 9.2. *Potential domain-specific adverse events*

This study is expected to pose minimal risk. The STS intervention is used for patients recovering from sepsis, LRTI, and other diseases. RPM interventions used in this domain are commonly used as routine care for other diseases. As a result, anticipated adverse events (AE) will be uncommon and include mild distress following survey administration and breach of confidentiality. Other AEs will be reported only where, in the opinion of the co-Principal Investigators, the event might reasonably have occurred as a consequence of a study intervention or study participation (see Core Protocol Section 12). Additionally, it is expected that a high proportion of critically ill patients who will be enrolled in this trial will experience mortality, substantial morbidity and readmissions. These endpoints are included in the primary and secondary endpoints. Stopping rules in the rare scenario that an intervention worsens these endpoints are included in

the Statistical Appendix and data regarding the primary endpoint stratified by intervention and select secondary endpoints will be provided to the DSMB.

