#### 8.5.1. Assessing the proportional odds assumption

Assessment of the proportional odds assumption will occur once all patients are enrolled, or the study is ended for futility of one or more active arms over STS. We will dichotomize the endpoint at each level of the PDHD outcome, summarizing the odds ratio for each dichotomization and plotting for visual inspection of equality. Meaningful shifts in odds ratios across the ordinal scale will be interpreted as evidence of non-proportionality.

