## 8.8. *Futility stopping*

The interventions selected for this proposal have been used in clinical care for other conditions (e.g., heart failure) and not shown to harm patients. Furthermore, RAR ensures that a higher proportion of patients randomized to one of the four intervention arms are randomized to the better-performing arms based on the results of the interim analyses. Thus, the likelihood of harm in our trial is low.

We considered the rare scenario that an arm performs worse than usual care, for which RAR will not change the allocation ratios. We therefore included a rule where an arm would be discontinued if the posterior probability of harm (odds ratio for home days  $< 1$ ) is  $> 90\%$ :

$$\text{Futility rule: } \Pr(OR < 1) > 0.9.$$

Based on preliminary simulations, we expect enrolling ~1200 patients before harm in this scenario is detected. Our simulations also ensured that our rule would prevent an arm to be dropped prematurely and likely to show benefit at the end of the trial.

Futility checking will occur at all interim analyses except the first to allow sufficient patient accrual into each treatment arm, preventing some probability of false declaration of futility. Futility is assessed separately for each individual care model arm. Declaration of futility for a particular arm during an interim analysis will trigger an early stopping of randomization to that arm, pending review by the DSMB. If all active arms are dropped for futility, then the entire trial would conclude early. The trial would conclude at the interim at which the final active arm was dropped. Our futility rule was selected by evaluating the operating characteristics of several rules via simulation (See Appendix, Section 12.5).

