#### 8.9.6. Final analysis of hospice care

Analysis of admission to hospice care will be performed using Bayesian Logistic regression with uninformative priors. The endpoint will be defined as any admission to hospice by day 90 post-discharge; any hospice care will be considered a successful outcome, while death within 90 days or survival without hospice care will be considered as non-successful outcome. The linear predictors the model will mimic that of the primary analysis in 8.3.3. From this model, we will estimate the following quantities:

- Posterior probability of superiority of each active arm over STS in terms larger odds of admission to hospice within 90 days.
- Posterior probability of superiority of each active arm over all other active arms in terms larger odds of admission to hospice within 90 days.

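### Section 9.2 says stopping rules cover worsening mortality and readmissions, but the only rule acts on the composite home-days odds ratio, which can sit near 1 when deaths rise and survivors gain home days

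*Combined protocol and SAP*

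**What the plan says.** Section 9.2 expects that a high proportion of patients "will experience mortality, substantial morbidity and readmissions. These endpoints are included in the primary and secondary endpoints". It continues: "Stopping rules in the rare scenario that an intervention worsens these endpoints are included in" the Statistical Appendix. It adds that the DSMB will receive the primary endpoint by intervention and select secondary endpoints, which it does not name.

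The rule itself is in Section 8.8: "an arm would be discontinued if the posterior probability of harm (odds ratio for home days" below 1) exceeds 90%. Section 8.4.4 computes that probability from the OR of the primary model, which has one proportional effect across all levels from -1 (death) to 90. On timing: "Futility checking will occur at all interim analyses except the first". A drop is subject to DSMB review.

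Section 8.5 accepts that effects on survival and on survivors' home days may differ. On checking this, Section 8.5.1 says: "Assessment of the proportional odds assumption will occur once all patients are enrolled, or the study is ended for futility". The model that separates death from home days (8.5.2) is a secondary analysis, placed in the final analysis (8.9.3).

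**The concern.** Section 9.2 can be read as saying that worsening of mortality or of readmissions would itself trigger a stopping rule. No rule in Section 8 or Appendix 12 uses death or readmission alone. A single proportional OR averages the effect on death with the effect on survivors' time at home, so one can offset the other. An arm with more deaths and better home days among survivors could then look neutral to the only formal harm criterion for the whole of accrual.

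The simulations do not settle this. Every OR in Table 3 is 1.0 or higher, and the non-proportional scenarios (Section 12.6, Tables 6 to 7.2) hold mortality fixed. No tabulated scenario raises deaths, so the performance of the harm rule under harm is not shown. Even for an arm that is worse than usual care on the composite, Section 8.8 says: "Based on preliminary simulations, we expect enrolling ~1200 patients before harm in this scenario is detected". Planned enrolment is now 1,281.

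**Working it through.** **Inputs.** Table 2 gives the baseline distribution: 0.133 for death, 0.005, 0.017, 0.017, 0.026, 0.042, 0.077, 0.228, and 0.454 for 90 days (rescaled, as it sums to 0.999). Section 12.2 gives the strata: severe 11% (OR 0.75) and SNF 37% (OR 0.35), independent. Arm sizes are STS 450 (Table 5.1) and an active arm of 262 (null averages are 249 to 268, Section 12.5). The rises in death odds are my assumption; the documents give none.

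**Reproducing the plan's figure.** Table 6, baseline, survivor OR 1.50, death unchanged. P(90 | alive) = 0.454/0.866 = 0.524. Odds of fewer than 90 days = 0.476/0.524 = 0.908, and 0.908/1.5 = 0.605. New P(90 | alive) = 1/1.605 = 0.623. Times 0.867 alive = 0.540. Table 6 states 0.54.

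**STS mortality.** Shifting the death odds by the strata ORs and weighting:

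| Stratum | Weight | STS mortality | At death odds x1.48 |
|---|---|---|---|
| Neither | 0.89 x 0.63 = 0.5607 | 0.133 | 0.185 |
| Severe | 0.11 x 0.63 = 0.0693 | 0.170 | 0.233 |
| SNF | 0.89 x 0.37 = 0.3293 | 0.305 | 0.394 |
| Both | 0.11 x 0.37 = 0.0407 | 0.369 | 0.464 |
| Weighted | 1 | 0.202 | 0.2685 |

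**Why the effects cancel.** Take the baseline stratum with death odds x1.48 and survivor OR 1.5. At the death cut the OR is 1/1.48 = 0.68. At the 90-day cut, P(90) = (1 - 0.185) x 0.623 = 0.508, so the OR is (0.508/0.492)/(0.4545/0.5455) = 1.24. The proportional-odds model averages across the cuts.

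**Pooled OR.** This is a maximum-likelihood proportional-odds fit to expected counts, adjusted for both strata. The chance that the rule trips at one look with full data is Phi(-ln(OR)/SE - 1.2816), with SE about 0.142.

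| Death odds | Survivor OR | Mortality | Pooled OR | Trip, one look |
|---|---|---|---|---|
| x1 | 1.0 | 20.2% | 1.00 | 10% |
| x1.5 | 1.0 | 27.1% | 0.80 | 63% |
| x2.0 | 1.0 | 32.8% | 0.66 | 95% |
| x1.25 | 1.25 | 23.8% | 1.01 | 9% |
| x1.25 | 1.5 | 23.8% | 1.12 | 2% |
| x1.48 | 1.5 | 26.85% | 1.00 | 10% |
| x1.5 | 1.5 | 27.1% | 0.99 | 11% |

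Over four to five looks at the SAP's 70 patients a month, the trip rates are about 19-21% for a null arm, 64-70% for x1.5 with survivors unchanged, 93-96% for x2.0 with survivors unchanged, and 20-23% for x1.5 with survivor OR 1.5.

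**A mortality-only comparison at the same one-sided 0.10 level**, 20.2% against 27.1%: SE under the null is sqrt(0.2273 x 0.7727 x (1/450 + 1/262)) = 0.0326. SE under the alternative is sqrt(0.2019 x 0.7981/450 + 0.2710 x 0.7290/262) = 0.0333. Power = Phi((0.0692 - 1.2816 x 0.0326)/0.0333) = 79%. The composite rule trips in 11% at the same single look when the survivor OR is 1.5.

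**Accuracy.** For survivor OR 1.5 with death unchanged, my fit gives a pooled OR of 1.28. Table 7.1 (All Expected) implies 1.50 - 0.26 = 1.24, and the plan's own null bias of -0.03 accounts for most of the gap. My null trip rate of 19-21% is below the roughly 25% per arm in Table 5.2, so the multi-look rates are approximate.

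**The case against.** The strongest reply is that Section 9.2 is true as written. It says that these outcomes are included in the primary and secondary endpoints, the primary outcome is a composite of mortality and morbidity, and days in hospital after readmission are subtracted from it. A rule on the composite therefore covers all three jointly. This stands in part. It makes the readmission side of the concern weak, and it means that Section 9.2 needs clarifying rather than withdrawing. It does not supply a criterion for mortality when the components move apart.

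Several stronger readings are tempting, and the documents do not support them.

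- *The rule is blind to death.* It is not. With survivors unchanged it trips far more often than under the null. Masking needs a survivor benefit of matching size: OR 1.23 for death odds x1.25, 1.53 for x1.5 and 2.46 for x2.0.
- *No one can see deaths during the trial.* The DSMB receives the primary endpoint by arm, in which deaths are coded -1, together with select secondary endpoints. It also reviews serious adverse events and any proposed arm drop. What is missing is a stated mortality summary and criterion.
- *Adaptive randomization would feed a harmful arm.* Sections 8.4.2 and 8.7 rank active arms against each other, not against STS. A pooled OR of 1.12 draws patients only if the other active arms look worse.
- *The Enhanced Team is likely to raise deaths.* Nothing in the documents says so, and the protocol expects a small effect on time to death. The hospice scoring in Section 8.9.6 ("any hospice care will be considered a successful outcome") belongs to a final secondary analysis and does not enter the harm rule.

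The Core Protocol was not supplied. Section 9.2 points to the Statistical Appendix, which I take to be SAP Section 8 and Appendix 12.

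**Conclusion.** The point holds in a limited form. Section 9.2 does not tell the reader that the one formal stopping rule acts on the composite home-days OR only. That rule responds to excess deaths alone, but it can miss excess deaths accompanied by a gain among survivors. At death odds x1.48 and survivor OR 1.5, mortality rises by 26.85 - 20.19 = about 6.7 points, the pooled OR is 1.00, and the rule behaves as it does for a null arm. Deaths may be noticed informally, but no mortality-specific criterion exists, and the separate mortality model waits for the final analysis.

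The pooled ORs rest on Table 2, the strata figures and the assumed death effects. The trip rates also rest on a normal approximation without adaptive allocation, time terms or factorial borrowing, at 1,500 patients rather than 1,281. This is a gap in monitoring and wording, not evidence that any arm is harmful.

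**What to change.** 1. In Section 8.8, at each interim from the second on, add a non-binding report to the DSMB: deaths by arm, and for each active arm the posterior probability that its mortality OR against STS exceeds 1, from a logistic model of death by day 90 with the same strata and time covariates as the primary model.
2. In Section 9.2, name mortality and readmissions among the select secondary endpoints that the DSMB receives.
3. In Section 9.2, state that the formal stopping rule acts on the composite home-days OR only.

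The cost is SAP wording and one extra model per interim, on data already collected. A report that never declares success should not materially raise the efficacy type I error. Tables 5.1 and 5.2 show the same 0.023 with and without the existing rule.

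The main downside is false alarms, so any flag threshold should be set with the DSMB. At 0.9, a null arm would be flagged at some look in about 25% of trials, as under the existing rule. For at least one of four null arms, independence would give 1 - 0.75^4 = 68%. Sharing the STS group lowers this to about 58% in a normal approximation with 11 looks, where the per-arm rate is 25%. With 5 looks the approximation gives 21% per arm and about 50% overall.

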### **9.3. Domain-specific consent issues**

Electronic, verbal, or paper-based consent for the study will be obtained during a hospital admission at various UPMC and non-UPMC sites. Research Team members, who have completed institution-specific Human Research Protection Office (HRPO) CITI trainings, will assist the subject in navigating the consent process. The consent process will provide subjects with a clear explanation of the objectives, procedures, risks and benefits of the study and their rights as study participants. A Frequently Asked Questions (FAQ) page will also be available to the subjects. Members of the Research Team begin the consent process by reading through an IRB approved script explaining the study and conduct a comprehension and cognitive screener. If the subject is interested and meets eligibility criteria, the Research Team can continue with obtaining consent. Written or verbal consent with a proxy may also be obtained through an IRB approved proxy consent process if the participant has an altered mental state (fails any of the screeners) but still wishes to participant in the study.

Research Team members will be available in-person, over the phone, or via video to answer all questions related to the informed consent process and study procedures prior to the subject consenting to participation. Consent for the qualitative interviews will also be obtained during this process.

Participants will retain their right to have their questions answered by Principal or Co-Investigators or a member of the Research Team via telephone or through any other preferred method of communication. The Research Team believes that informed consent is an ongoing process in any study and so will continue to educate participants about the nature of the research and will address any questions that arise throughout the course of the study. These efforts will comply fully with the Health Insurance Portability and Accountability Act (HIPAA) and the informed consent guidelines of the University of Pittsburgh IRB.

## **10. FUNDING**

### **10.1. Funding of domain**

The ACCOMPLISH domain is funded by the Patient Centered Outcomes Research Institute, contract #IHS-2019C1-16055.

### **10.2. Funding of domain interventions**

The STS and RPM interventions in the ACCOMPLISH domain are funded by UPMC.

**10.3. *Domain-specific declarations of interest***

All investigators involved in REMAP Post-Acute Care ACCOMPLISH domain maintain a declaration of conflicting interests with the Patient-Centered Outcomes Research Institute.

## 12. Appendix

### 12.1. *Sepsis data for simulations*

To create realistic clinical trial simulations, we obtained pre-trial member-level data from UPMC for patients that were hospitalized from either sepsis, pneumonia, and/or a lower respiratory infection. Patients in this sample were at least 21 years old and deemed low risk for readmission (based on an internal UPMC risk score). We received 4718 records from members that received their insurance through Medicare or commercial plans. This data included the following covariates: age group, CCI, sepsis status, pneumonia status, LRTI status, whether a patient had mechanical ventilation, vasopressors, or was in the ICU. In addition, we have whether a patient was discharged to a SNF or to home, as well as their home days endpoint score. We additionally received 2737 records from members whose insurance is through Medicaid or SNP (special needs population). This data only contained the home days endpoint with no additional covariate information.

Using the totality of this data, we summarize the home days distribution by finding the proportion in each level of the outcome, as shown in the “Overall” column in Figure 2.

In addition, we summarize the two strata variables using the partial data with covariate information. We define the severe strata as patients who were on mechanical ventilation or vasopressors during their hospital stay. In this data, 11% of the population meets this definition. We define the SNF population as patients whose discharge status was “Discharge to SNF”, where 37% of the population meet this definition. Using these covariates, we estimate the relationship between the home days endpoint and the covariates, illness severity and discharge to SNF, using a frequentist ordinal regression. We estimate an odds ratio for severe illness compared to non-severe of 0.75 and an odds ratio for patients discharged to SNF compared to those discharged home to be 0.35. Under these estimated odds ratios, we transform the home days distribution (using the full data) for the severe strata and the discharged to SNF strata. The resulting distributions are presented in Figure 2. Patients who are not categorized as severe or were discharged straight to home are assumed to have the baseline home days distribution shown in the overall column.

Strata variables were chosen empirically by evaluating the covariates that best explained patient heterogeneity in the data. These two variables were identified as major risk factors for this patient population using the provided data, therefore, were critical to control baseline characteristics.

[figure not shown]

Figure 2: Distribution of home days endpoint using UPMC member level data.

12.2. Virtual patient simulation

In these simulations, we simulate a maximum total sample size of 1500 patients assuming no patient dropout. For each simulation, we assume the ACCOMPLISH trial will enroll 11% of patients that are in the severe strata and 37% of patients that are discharged to SNF (using proportions from the observed data). We simulate the strata by drawing from two independent Bernoulli variables with probability 11% for the severe strata variable and 37% for the SNF variable. These strata are not mutually exclusive such that a patient may be both severe and discharged to SNF. Based on a patient's strata assignment, we shift the overall home days distribution using the odds ratios of 0.75 and 0.35 for severe and discharged to SNF strata, respectively. If a patient is both severe and discharged to SNF, their home days distribution is shifted with an odds ratio of 0.26 ( $\exp(\log(0.75) + \log(0.35))$ ). We do not incorporate the additional covariates (age categories) into the simulations since we do not expect age to influence the treatment effect and therefore the operating characteristics of the trial.

To simplify the simulations, we assume a collapsed distribution of home days. Table 2 shows the collapsed distribution for the baseline population.

**Table 2. Collapsed home days distribution for the baseline population**

| Death | 0-19  | 20-39 | 40-49 | 50-59 | 60-69 | 70-79 | 80-89 | 90    |
|-------|-------|-------|-------|-------|-------|-------|-------|-------|
| 0.133 | 0.005 | 0.017 | 0.017 | 0.026 | 0.042 | 0.077 | 0.228 | 0.454 |

For patients in strata, this distribution is then shifted based on the ORs described above.

### 12.3. *Simulated treatment effect scenarios*

We assume proportional odds treatment effects for each care model under different patterns of efficacy. Table 3 presents the scenarios in terms of the OR on each of the 4 care models. Table 4 summarizes the endpoint for each stratum under each of these assumed OR treatment effects.

**Table 3. Treatment effect scenarios**

|    |                                 | RPM low +
Standard | RPM high +
Standard | RPM low +
Enhanced | RPM high +
Enhanced |
|----|---------------------------------|-----------------------|------------------------|-----------------------|------------------------|
| 1  | Null                            | 1.0                   | 1.0                    | 1.0                   | 1.0                    |
| 2  | One Weak                        | 1.0                   | 1.0                    | 1.0                   | 1.25                   |
| 3  | One Expected                    | 1.0                   | 1.0                    | 1.0                   | 1.5                    |
| 4  | One Strong                      | 1.0                   | 1.0                    | 1.0                   | 1.75                   |
| 5  | Two Weak                        | 1.0                   | 1.25                   | 1.0                   | 1.25                   |
| 6  | Two Expected                    | 1.0                   | 1.5                    | 1.0                   | 1.5                    |
| 7  | Two Strong                      | 1.0                   | 1.75                   | 1.0                   | 1.75                   |
| 8  | All Weak                        | 1.25                  | 1.25                   | 1.25                  | 1.25                   |
| 9  | All Expected                    | 1.5                   | 1.5                    | 1.5                   | 1.5                    |
| 10 | All Strong                      | 1.75                  | 1.75                   | 1.75                  | 1.75                   |
| 11 | All Weak, Combo
Additive     | 1.25                  | 1.25                   | 1.25                  | 1.56                   |
| 12 | All Expected, Combo
Additive | 1.5                   | 1.5                    | 1.5                   | 2.25                   |
| 13 | All Strong, Combo
Additive   | 1.75                  | 1.75                   | 1.75                  | 3.06                   |

